### Blinding procedures

The study participant, study physician, principal investigator, sponsor, study nurse, data manager and biometrician, as well as the qualitative researcher, will be blinded to treatment. To ensure blinding, the study pharmacy will produce placebo preparations that are, after labeling, indistinguishable from the study medication.

The possibility of unblinding in emergency situations (e.g., when necessitated by an SAE) is ensured during the study. Sealed emergency envelopes with the treatment assignments will be prepared by an independent data manager at the sponsor’s site, who is otherwise not involved in the study.

### Randomization

Patients will be randomized by block randomization with randomly varying block lengths, stratified by study center. Patients will be randomized into one of the three groups (standardized homeopathy, individualized homeopathy, or placebo) in a 1:1:1 ratio using “R” software (The R Foundation, Free Software Foundation, Version 3.6.1, Boston, USA). The randomization list will be generated by a biometrician at the sponsor’s site, who is otherwise not involved in the statistical analysis of the study and has no access to study data. The results of the randomization will be integrated into a database (Microsoft ACCESS 2016, Redmont, USA) by an independent data manager, who is also responsible for the creation of the emergency envelopes but is otherwise not involved in the study. The patient code and the group allocation will be generated by the pharmacy during randomization (in an ACCESS database). Based on this database, the study pharmacy will allocate the patients into one of the homeopathic drug treatment groups. The group allocation will be known only to the pharmacist and one independent unblinded data manager who is not further involved in the study organization. If a patient withdraws from the study, the randomization number assigned to them may not be assigned again; withdrawn patients will not be eligible for study re-entry at a later point in time.

### Sample Size calculation

The study is designed to detect a minimal clinically important difference (MCID) between either one of the two drugs and the placebo group with 80% power. For the RQLQ, the MCID is 0.5 points [25]. The common standard deviation, based on baseline data from an earlier study [27], is estimated at 1.1, corresponding to an effect size of d = 0.45. With these assumptions, *n* = 77 patients per treatment group are needed (i.e., a total of *n* = 231 patients in three treatment groups). To compensate for up to a 15% dropout rate [27], we plan to randomize *n* = 270 patients (i.e., *n* = 90 per treatment group).

### Statistical analysis

Analyses will be performed for 4 populations. (1) An intention-to-treat (ITT) population, including all randomized patients regardless of whether data are available, whether the intervention was performed according to the protocol, whether unauthorized concomitant interventions were undertaken, or whether any other protocol violations occurred. Every patient will be analyzed as if they had conducted the trial according to the group to which they were originally allocated. Missing values in primary and secondary outcomes will be imputed using multivariate imputation by chained equations (MICE). (2) A per-protocol population (PPP) will include only patients with no major protocol deviations. (3) A safety set, including all randomized patients who receive at least one dose of the study drug, will be analyzed according to the study drug they received. (4) A safety set without taking comedication, will include all patients who received at least one dose of their allocated drug and did not take rescue medication or any other medication during the study period and will be analyzed as treated.

Sociodemographic and medical baseline data will be analyzed descriptively in terms of the mean, standard deviation, median, minimum, and maximum for continuous data or in terms of frequencies and percentages for categorical data (for each treatment group and in total).

The primary endpoint is defined as the mean of the RQLQ total score at the end of weeks 3 and 4. A closed testing procedure [31] will be used for the primary outcome to handle the pairwise comparisons between 3 treatment groups to control the overall type I error and to maintain the global significance level of α = 5% (two-sided). First, a global test will be used across all 3 treatment groups to test the null hypothesis of equal means. If this null hypothesis is rejected, two pairwise comparisons (individual homeopathy vs. placebo, standardized homeopathy vs. placebo) will be tested confirmatively. The comparison of individualized homeopathy vs. standardized homeopathy will be tested exploratively. The analysis will be performed on the ITT population using an analysis of covariance (ANCOVA), in which the endpoint is modeled as a function of treatment group (fixed factor), baseline RQLQ score (linear covariate), and the study center (random factor) to obtain the treatment group means, mean treatment group differences, respective 95% confidence intervals, and the (two-sided) p values. All secondary endpoints will be analyzed exploratively using both the ITT and PPP analysis sets. Continuous secondary endpoints will be analyzed by ANCOVA, in which the endpoint is modeled as a function of treatment group (fixed factor), the baseline value of the respective variable (linear covariate), and the study center (random factor) to obtain the mean treatment group differences, the 95% confidence intervals, and the explorative p values (two-sided). Responder rates will be compared between treatment groups using logistic regression adjusted for the baseline RQLQ value and the study center (random factor).

Safety endpoints will be analyzed descriptively for the two safety sets.

The monetary evaluation of resource use will be undertaken using German standardized cost rates. The results will be tested for relevant and statistically significant differences as part of a cost comparison analysis between the treatment groups. Additionally, QALYs will be calculated based on the results of the SF-12 questionnaire and used for a cost-effectiveness analysis. In case of the superiority of a treatment group in terms of QALYs, the incremental costs per QALY gained (ICER) will be obtained by combining cost and effect differences between treatment groups. In the case of increased costs and improved quality of life, the ICER indicates the cost-effectiveness by adopting an internationally accepted threshold (e.g., ≤ 50.000 Euro per QALY gained). Besides QALYs, further outcomes, including RQLQ changes and number of responders, will be used for estimating the total treatment costs. All cost-effectiveness results will be visualized in a cost-effectiveness plane.

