## Methods

### Study design

HOMEOSAR (Homeopathy for Seasonal Allergic Rhinitis**)** is a three-armed, phase IV, randomized, parallel group, placebo-controlled, double blind, multicenter interventional trial for patients suffering from SAR. The study will be conducted for 8 weeks per patient, including a treatment phase of 4 weeks and a follow-up observational phase of 4 weeks (Fig. 1). By including a qualitative component, the study will follow a mixed methods approach. The Recommendations for Interventional Trials (SPIRIT) 2013 [22, 23] were also followed in the design of this trial.

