Patients in all treatment groups may take second-generation oral antihistamines (10 or 20 mg cetirizine) on demand as rescue medication. In case when a daily maximum dose of 20 mg cetirizine is not sufficiently effective, patients may additionally take an oral cortisone preparation (max. prednisolone 10 mg/day). During the 8-week study period, patients are asked not to use any concomitant homeopathic treatment or any other complementary and integrative medical treatments (e.g., herbal medicine, acupuncture, and others) for the treatment of SAR symptoms.

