**Fig. 3 Fig3:**
[figure not shown]
Standard Protocol Items: Recommendations for Interventional Trials (SPIRIT) Figure. Abbreviations: *RQLQ*  Rhinitis Quality of Life Questionnaire, *VAS SAR*  Visual analog scale of seasonal allergic rhinitis symptoms, *SF-12*  Generic health-related quality of life questionnaire Short Form 12, *TNSS*  Total Nasal Symptom Score, *RMS*  Rescue Medication Scor e

The RQLQ is a well-established and validated questionnaire developed by Juniper et al. [24, 25]. It has been used successfully as a primary [15, 26–28] or secondary endpoint [29] in numerous studies of high methodological quality. The RQLQ consists of 28 questions in 7 domains, including activity limitation, sleep problems, nose symptoms, eye symptoms, other symptoms, practical problems, and emotional state, ranked from 0 (no impairment) to 6 (severe impairment). The RQLQ also captures nasal symptoms as a standard endpoint for allergic reactions [30].

Secondary outcome measures will be measured at the end of weeks 2, 3, 4, 7, and 8 and will include the RQLQ overall score and the seven RQLQ domain scores, nasal symptoms (Total Nasal Symptom Score, TNSS), the use of rescue medication (Rescue Medication Score, RMS), and SAR symptoms (nasal and nonnasal, 100 mm VAS ranging from 0 mm = no symptoms to 100 mm = max. symptoms). The responder status is defined by at least a 0.5-point decrease (improvement) in the RQLQ overall score (mean of weeks 3 and 4) compared to the baseline value. The generic health-related quality of life (SF-12) questionnaire will be used to assess the perceived homeopathic drug treatment effect on generic quality of life and to measure quality-adjusted life years (QALYs). For the health economic analysis, the patient-specific use of health care resources during the study (doctor contacts, hospital stays, medication, remedies and aids, work absence and incapacity days) will be documented continuously, and the associated costs will be calculated. Combined with the results on QALYs, a cost-effectiveness assessment of the study treatment will be carried out. Adverse events (AEs), serious adverse events (SAEs), and the number of patients who discontinue treatment due to AEs or SAEs will be collected from baseline until completion of the study.

In the qualitative part of the study, the subjective experiences of treatment, treatment satisfaction and subjectively perceived effects of the treatment will be assessed.

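### Safety set (4) drops any patient who took any medication during the study, so drug-treated adverse events leave that set with their patients; safety set (3) is unaffected

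*Protocol article*

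**What the plan says.** The Statistical analysis section of the protocol article names two safety populations.

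- Set (3): "A safety set, including all randomized patients who receive at least one dose of the study drug", analyzed by drug received, with no condition on other medication.
- Set (4): "A safety set without taking comedication, will include all patients who received at least one dose of their allocated drug" and who "did not take rescue medication or any other medication during the study period", also analyzed as treated.

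Both are used: "Safety endpoints will be analyzed descriptively for the two safety sets".

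Three other sections matter here.

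- Study design sets the period: "The study will be conducted for 8 weeks per patient, including a treatment phase of 4 weeks and a follow-up observational phase of 4 weeks".
- Outcome measures states that AEs, serious AEs and discontinuations due to them "will be collected from baseline until completion of the study".
- Intervention and rescue medication allows rescue in every arm: "Patients in all treatment groups may take second-generation oral antihistamines (10 or 20 mg cetirizine) on demand as rescue medication", with an oral cortisone preparation possible in addition.

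**The concern.** Membership of set (4) is settled by what happens after randomization and, for some patients, after the AE itself. A patient who takes a painkiller for a headache is removed, and the headache goes with the patient. The rule has no carve-out for such treatment, is not limited to allergy drugs, and does not ask whether the medication came before or after the event. Serious AEs treated with a drug are removed with certainty.

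There is a second selection. Rescue use follows symptoms, and symptoms are what the study drugs are meant to change. If an active drug works, more of its patients stay in set (4) than on placebo, and those who stay differ systematically by arm.

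At stake is one of the two planned safety tables. It would tend to show the patients who had no event worth treating, and side-by-side arm columns would invite a comparison that randomization no longer supports.

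**Working it through.** **Timing.** The exclusion covers the study period, which is 8 weeks. AEs are collected from baseline to completion. The two windows coincide, so medication taken because of an AE falls inside the exclusion window.

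**Direction and size.** The article gives no AE rate and no expected size for set (4), so there is no figure to reproduce. All rates below are assumptions, shown over a range. Let

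- a = true proportion of patients with an AE,
- t = share of patients with an AE who are medicated for it,
- m = probability of other medication use (rescue included), taken as independent of AEs.

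The proportion with an AE among those kept is

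a(1−t)(1−m) / [a(1−t)(1−m) + (1−a)(1−m)] = a(1−t) / (1−at).

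The term m cancels: unrelated medication use shrinks the set without shifting the rate. The result is below a whenever t > 0. For a = 20% and t = 50%: 0.20 × 0.5 / (1 − 0.10) = 0.10 / 0.90 = 11.1%.

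| True AE proportion | t = 25% | t = 50% | t = 75% | t = 100% |
|---|---|---|---|---|
| 10% | 7.7% | 5.3% | 2.7% | 0% |
| 20% | 15.8% | 11.1% | 5.9% | 0% |
| 30% | 24.3% | 17.6% | 9.7% | 0% |

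With t = 0 there is no shift.

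**When the shift would vanish.** If other medication use differs by AE status, the downward shift disappears only when AE-free patients use it more: m(no AE) = 1 − (1−t)(1−m(AE)). With t = 50% this means 75% use in AE-free patients against 50% in patients with an AE, or 90% against 80%. Nothing in the article suggests such a pattern.

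**Set size.** Patients kept per arm, out of the planned 90: 90 × (1−m) × (1−at). At a = 20% and t = 50%, this is 90 × 0.5 × 0.9 = 40.5 if half use other medication, and 90 × 0.2 × 0.9 = 16.2 if 80% do. With 80% use and no loss through treated AEs, 90 × 0.2 = 18 remain. Zero events among 18 would still be compatible with a true risk of 1 − 0.05^(1/18) = 15.3% (one-sided 95% bound). High rescue use is plausible, since eligibility requires an indication for oral antihistamines and rescue medication is handed out at baseline, but the article states no rate.

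**Can membership be established?** Under Study procedures, the rescue diary runs from baseline to the end of week 4 and again in weeks 7 and 8. Weeks 5 and 6 are not covered. Outcome measures says medication use is documented continuously for the health economic analysis, but does not say that start dates are recorded. The diary alone therefore cannot settle who took nothing over the whole study.

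**The case against.** The strongest reply is that the unselected analysis is already planned. Every AE, medicated or not, appears in set (3), and both sets are reported. Safety is descriptive, so no test and no type I error is affected, and no between-arm safety estimate is planned. All of this stands. A reader might infer from the definition of set (4) that the trial's safety reporting as a whole understates harm; the article does not support that, because set (3) is not conditioned on medication.

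A second reply is that set (4) is openly labelled as patients without co-medication, plausibly to show AEs that cannot be due to the rescue drugs. AEs caused by those drugs are meant to drop out, so a rate below that in set (3) is partly intended. This stands as well, and it means the gap between the two sets cannot all be called bias. But the rule does not serve that purpose well: it also discards AEs that occurred before any co-medication, which are the events most informative about the study drug alone.

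A third reply is that the size is unknown. This is correct. The percentages rest on assumed AE rates, on an assumed share medicated, and on other medication use being unrelated to AEs. AEs that are not treated with a drug are not removed by this mechanism.

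Finally, splitting follow-up at the first co-medication dose still conditions on symptom-driven behaviour. That also stands. The remedy keeps drug-treated AEs in the count but does not restore randomized groups.

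**Conclusion.** The point holds for set (4) only. As worded, its exclusion rule removes drug-treated AEs with their patients, and its arms are not randomized groups. The downward shift in AE proportions follows if some AEs are medicated and other medication use is unrelated to AEs. An assumed 20% risk would show as 11% with half of the AEs medicated, and as 16% to 6% as that share goes from 25% to 75%. These are illustrations, not estimates for this trial.

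It would be tempting to say that the set is biased downward under any circumstances. The article does not support that either: the size depends on rates that it does not give, and a strong opposite link between AEs and other medication use could offset the effect in theory. The primary analysis and the AE rates in set (3) are untouched. This is a limited flaw in a descriptive population, worth correcting because the correction is small.

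**What to change.** 1. Name set (3) as the main safety analysis.
2. Replace the whole-period exclusion in set (4) with a time-ordered rule. A patient's AEs count from the first study dose up to the first dose of co-medication, and medication started to treat an AE does not remove that AE. Give patient-days alongside the counts, because the time contributed will differ between patients.
3. Limit this analysis to the 4-week treatment phase, where the rescue diary is daily and without the gap in weeks 5 and 6. Apply the rule to other medication only where start dates are recorded.
4. Label the result supplementary and state that it is not a randomized comparison.

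A smaller alternative keeps set (4) and adds one sentence saying that medication given for an AE does not exclude the patient. It repairs the removal of treated AEs but leaves the reliance on whole-period medication records, and still discards AEs that came before unrelated co-medication.

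The cost is a change of wording and slightly more programming, with no new data for rescue medication in the treatment phase. Follow-up in set (4) becomes shorter, and off-medication time is still selected by symptoms. The study drug may start up to 5 days after the first consultation, so patients who use rescue before their first study dose would contribute no time; their number should be reported per arm.

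### The cost-per-QALY ratio depends on an undefined superiority in QALYs; if that means significance, it will often be missing and, when given, rests on average on an overstated gain

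*Protocol article*

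**What the plan says.** All of this is in the protocol article, Methods, Statistical analysis, in the health-economic paragraph unless noted.

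- Costs: "The results will be tested for relevant and statistically significant differences as part of a cost comparison analysis between the treatment groups". No condition is attached.
- QALYs: "QALYs will be calculated based on the results of the SF-12 questionnaire and used for a cost-effectiveness analysis".
- The ratio: "In case of the superiority of a treatment group in terms of QALYs, the incremental costs per QALY gained (ICER) will be obtained", by combining the cost and effect differences between groups.
- The threshold: "In the case of increased costs and improved quality of life, the ICER indicates the cost-effectiveness by adopting an internationally accepted threshold", with 50,000 Euro per QALY gained as the example.
- Other outcomes: "Besides QALYs, further outcomes, including RQLQ changes and number of responders, will be used for estimating the total treatment costs".
- Display: "All cost-effectiveness results will be visualized in a cost-effectiveness plane".

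Elsewhere, the Study design section says "The study will be conducted for 8 weeks per patient". The Sample Size calculation section rests on the RQLQ only. The Statistical analysis section makes all secondary endpoints exploratory.

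**The concern.** Cost-effectiveness is a statement about two differences taken together. Whether the QALY difference passes a criterion on its own does not decide whether the pair is good value. An arm with a small, unproven gain and little or no extra cost may be worth having, yet under a significance condition it would get no ratio.

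The condition also selects. If the ratio is formed only after a favourable QALY result, the gains in its denominator are too large on average. At a given positive cost difference the ICER is then too low, which favours passing the threshold.

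Superiority is not defined, and the sentence comes shortly after one that tests costs for significance, so a significance condition is a natural reading. A higher-mean reading is also possible. The two behave very differently, and the choice between them could be made after the data are seen.

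**Working it through.** **1. The plan's own sample size.** Inputs from the Sample Size calculation section: difference 0.5, SD 1.1, power 80%, 15% dropout. The two-sided 5% level is stated for the primary outcome.

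n per arm = 2 × (1.960 + 0.842)² × (1.1/0.5)² = 76 by the normal formula, and 76.95, so 77, by the t-test. The stated 77 is reproduced. For dropout, 77/0.85 = 90.6 against the stated 90, an immaterial difference. No QALY effect, SD or power is given.

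**2. How the condition behaves.** Take one active arm against placebo, n = 77 per arm, and a normal approximation. Let d be the true QALY difference divided by its SD (after any baseline adjustment). The document does not give d, so a range is assumed.

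- Expected test statistic: δ = d × √(77/2) = 6.205 d.
- Chance that the ratio is reported: 1 − Φ(c − δ), with c = 1.96 if superiority means two-sided p < 0.05 in favour of the arm, and c = 0 if it means a higher mean.
- Average reported gain relative to the true gain: [δ + φ(c − δ)/(1 − Φ(c − δ))]/δ.

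Worked case, d = 0.2 under significance: δ = 1.241; 1 − Φ(0.719) = 0.236; φ(0.719) = 0.308; (1.241 + 0.308/0.236)/1.241 = 2.05.

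| d | p < 0.05: reported | inflation | higher mean: reported | inflation |
|---|---|---|---|---|
| 0 | 2.5% | all spurious | 50% | all spurious |
| 0.1 | 9.0% | 3.91 | 73.3% | 1.72 |
| 0.2 | 23.6% | 2.05 | 89.3% | 1.17 |
| 0.3 | 46.1% | 1.46 | 96.9% | 1.04 |
| 0.4545 | 80.5% | 1.12 | 99.8% | 1.00 |

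With all 90 randomized per arm, the significance column for d = 0.1, 0.2 and 0.3 becomes 9.9%, 26.8% and 52.1%, with inflation 3.63, 1.92 and 1.38. If both active arms have the same d, the chance that at least one passes at n = 77 is 15.2%, 36.1% and 62.7%.

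**3. On the QALY and Euro scale.** Assume an SD of 0.10 for mean utility over the 8 weeks. Then d = 0.1, 0.2 and 0.3 are utility differences of 0.01, 0.02 and 0.03. Multiplying by 8/52 = 0.154 years gives gains of 0.00154, 0.00308 and 0.00462 QALY, worth 77, 154 and 231 Euro at 50,000 Euro per QALY.

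The smallest significant gain is 1.96 × 0.10 × √(2/77) × 0.154 = 0.00486 QALY, worth 243 Euro. For an assumed SD of 0.08 to 0.15 it runs from 0.00389 to 0.00729 QALY.

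So with a true gain of 0.00308 QALY, the extra cost that just meets the threshold is 154 Euro. Every ICER that passed the significance condition would divide by at least 0.00486. An extra cost anywhere between 154 and 243 Euro would then be judged acceptable in every reported case, although it is above the threshold.

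**4. Without the condition.** The result is reported in 100% of trials and the QALY difference is not selected upward (ratio 1.00).

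**The case against.** The strongest objection is that the document never says superiority means significance. Its next sentence, on higher costs with better quality of life, is ordinary quadrant logic: form a cost per QALY gained where QALYs are gained. Read that way, the rule is largely benign unless the effect is very small. This stands, and it is why the finding is conditional on the reading. If any group, placebo included, may be the superior one, a ratio is available for nearly every pair under the higher-mean reading.

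A reader might infer more than the document supports:

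- *That the economic question goes unanswered.* It does not. The cost comparison, the RQLQ and responder outcomes and the plane are planned without this condition. But only a cost-per-QALY result can be set against the stated threshold.
- *That the ratio appears only when the gain is overstated.* This would need both the significance reading and a true effect below 1.96/6.205 = 0.316 SD, where every significant estimate exceeds the truth. Above that, overstatement holds only on average, and at d = 0.4545 it is 1.12-fold. The document establishes neither condition.
- *That 8 weeks is too short to show superiority.* Duration scales the gain and its SD alike and leaves d, and so power, unchanged.
- *That any gain below the 80%-power difference would usually miss.* The chance falls below one half only under 1.96/2.80 = 0.70 of that difference.
- *That QALYs are separately tested.* The paragraph states a test for costs only.
- *That joint uncertainty has been left out.* A condensed article may leave bootstrap, net benefit and acceptability methods to the full plan. Their absence is not counted here.

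It can also be said that a significance condition guards against near-zero denominators. It does, but at the price of selection. Net monetary benefit has no denominator and avoids the problem without a condition.

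**Conclusion.** The point holds as a minor one. The article fixes a rule that makes its cost-per-QALY result depend on an undefined criterion. At an assumed d of 0.1, the two readings move the chance of a reported ratio from 9% to 73%. Under significance, for d from 0.1 to 0.3, the result is missing in 54% to 91% of trials and, when present, rests on a gain overstated on average 1.5- to 3.9-fold. Under a higher mean, it is missing in 3% to 27% and overstated 1.04- to 1.7-fold.

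These figures rest on assumed QALY effects, a normal approximation, 77 per arm and a single comparison with placebo. At d near 0.45 the problem is small under either reading. The economic analysis is secondary and exploratory, and the RQLQ conclusion does not depend on it.

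**What to change.** Delete the superiority condition. For every pairwise comparison:

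- Report incremental costs and incremental QALYs, the latter adjusted for baseline utility, whatever their sign or significance.
- Resample both together by bootstrap and show the replicates on the planned cost-effectiveness plane.
- Judge the threshold by net monetary benefit, 50,000 Euro × QALY difference − cost difference, with a 95% confidence interval, or by an acceptability curve.
- Give the ICER only as a descriptive point value where it is interpretable, with no decision resting on it.

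The cost is a change of wording and a standard bootstrap on data already to be collected. The drawback is that the economic conclusion may have to be stated with wide uncertainty.
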